# Hydrotherapy and acupressure in restless legs syndrome: A randomized, controlled, 3-armed, explorative clinical trial

**DOI:** 10.1097/MD.0000000000034046

**Published:** 2023-06-30

**Keywords:** acupressure, complementary and integrative medicine, hydrotherapy, Kneipp therapy, randomized controlled trial, restless legs syndrome, study protocol

## Abstract

**Methods::**

This is a randomized, controlled, open-label, exploratory, clinical study with 3 parallel arms, comparing both self-applied hydrotherapy (according to the German non-medical naturopath Sebastian Kneipp) and acupressure in addition to routine care in comparison to routine care alone (waiting list control) in patients with RLS. Fifty-one patients with at least moderate restless-legs syndrome will be randomized. Patients in the hydrotherapy group will be trained in the self-application of cold knee/lower leg affusions twice daily for 6 weeks. The acupressure group will be trained in the self-application of 6-point-acupressure therapy once daily for 6 weeks. Both interventions take approximately 20 minutes daily. The 6-week mandatory study intervention phase, which is in addition to the patient preexisting routine care treatment, is followed by a 6-week follow-up phase with optional interventions. The waitlist group will not receive any study intervention in addition to their routine care before the end of week 12. Outcome parameters including RLS-severity, disease and health-related quality of life (RLS-QoL, SF-12), Hospital Anxiety and Depression Score in German version, general self-efficacy scale, and study intervention safety will be measured at baseline and after 6 and 12 weeks. The statistical analyses will be descriptive and exploratory.

**Conclusion::**

In the case of clinically relevant therapeutic effects, feasibility, and therapeutic safety, the results will be the basis for planning a future confirmatory randomized trial and for helping to develop further RLS self-treatment concepts.

## 1. Introduction

### 1.1. Background and rationale

Restless legs syndrome (RLS), also known as Willis-Ekbom disease (WED), is a common neurological disorder characterized by agonizing sensations in the legs, occurrence at rest, and compelling urge to move the legs (or arms or sometimes other body parts).^[1]^ The diagnosis is primarily made by taking a clinical history (essential questions) and can be obtained by any physician, regardless of their specialty. RLS is a common disorder with a significant impact on daily activities and quality of life. Circadian fluctuations in RLS symptoms, with main symptoms in the evening and at night, often cause severe sleep disturbances and deprivation.^[2–4]^

RLS symptoms of any frequency and severity occur in 5% to 10% of the general population in Western industrialized countries.^[5–7]^ Approximately 1 in 4 RLS sufferers is aware of the diagnosis, and overall, 1 in 5 RLS sufferers desire drug treatment to relieve symptoms effectively.^[8]^

RLS affects and interacts with many comorbidities, and may lead to missed work, loss of social networks, and even early retirement.^[9,10]^ The impact of RLS can be very severe, and the quality of life of those affected is generally worse than that of other chronic diseases, such as type 2 diabetes, depression, and osteoarthritis.^[11]^ Although cost studies have shown certain limitations (the use of self-administered questionnaires), the results show that the costs related to RLS are substantial.^[12]^

Patients with RLS also show more anxiety and depression symptoms, psychopathological symptoms, and lower well-being than control subjects without sleep disorders. There is a relationship between RLS severity, anxiety, and depressive symptoms. Under psychological stress, RLS/WED symptoms are more severe.^[13,14]^

RLS is a complex disorder in which predisposing genetic factors, environmental factors, and comorbidities contribute to the expression of the disorder. Patients with a high burden of comorbidity have a consistently higher prevalence of RLS than healthy individuals do. Additionally, an increasing number of publications have reported associations between RLS and multiple diseases, including metabolic diseases (diabetes mellitus and iron deficiency), cardiac and renal diseases, autoimmune diseases (e.g., multiple sclerosis), polyneuropathy, neurodegenerative diseases (e.g., Parkinson disease), and illnesses associated with inflammation and depression.^[2]^

In many cases, RLS remains incurable; therefore, available treatments focus on alleviating the symptoms of the disease.^[2]^ However, the side effects of currently used medications, such as dopaminergic agents and non-ergot- and ergot-derived dopamine agonists, may lead to other health problems. The most important side effect is the so-called augmentation, that is, the amplification of RLS symptoms, which occurs in 30% to 68% of patients taking dopaminergic drugs.^[15]^ Other typical side effects of dopamine agonists, especially during the first few weeks of treatment, include edema, nausea, orthostatic dysregulation, dizziness, and lightheadedness.^[16]^

Dopamine agonists may also lead to impulse control disorders in up to 12.4% of patients taking the dopamine agonist Pramipexole).^[17]^ Other non-dopaminergic drug classes for the treatment of RLS, such as opioids, anticonvulsants, and alpha-adrenergic agonists (Clonidine), also have typical and well-known side effects, such as dizziness, somnolence, tremor, headache, mental changes, nausea, vomiting, urinary retention, and constipation, which often lead to therapeutic limitations. The addictive potential of opioids is another therapy-limiting and health-threatening issue.^[18–22]^

Effective non-drug symptom reduction in RLS would be clinically helpful and relevant because RLS-medications with potential side effects, such as augmentation, could be avoided or reduced. State of the art reviews on RLS^[23]^ recommend that all non-drug treatment options be exhausted before starting drug treatment. According to the guidelines of the International Group Task Force, increases in medication over the course of treatment should be limited to the onset of clinically important symptoms that cannot be managed behaviorally.^[24]^

For the treatment of mild and intermittent forms of RLS, clinical guidelines often recommend relaxation methods and other non-pharmacological therapies.^[24–26]^ Recommendations are generally nonspecific and there is little meaningful research evidence.^[27,28]^

Up to 65% of RLS patients regularly use complementary medical interventions to relieve their symptoms and improve well-being.^[29]^

Hydrotherapy according to Kneipp and acupressure are methods of complementary and integrative medicine that can be performed by the patients themselves and at a low cost. To date, no randomized controlled trials have examined the effectiveness, safety, and feasibility of self-administered acupressure and hydrotherapy according to Kneipp in patients with RLS.

Two systematic reviews in 2019 and 2021 showed that acupuncture was significantly superior to control interventions for RLS in terms of severity and reported significant clinical effects.^[27,30–32]^ While acupuncture requires a trained therapist to stimulate specific acupoints with needles, acupressure involves massaging the same acupoints with fingers or hands, making it suitable for self-application.

In a pilot study on the efficacy of acupressure in dialysis patients with RLS, a reduction in RLS severity was reported.^[33]^ Several studies have demonstrated that acupressure can improve sleep-related symptoms, depression, anxiety, stress, pain, and psychological distress.^[34–40]^

Hydrotherapy according to Sebastian Kneipp (1821–1897) is characterized by serial, mostly cold-water applications (e.g., affusions, compresses, washes) and has been known in German-speaking countries since the 19^th^ century for preventive health care and the treatment of various diseases.^[41]^

There are indications that cold water applications can reduce RLS symptoms in pregnant women,^[42]^ and cold applications in general can produce an overall reduction in sleep-related symptomatology.^[27,30,32]^ Kneipp therapy showed significant improvements in sleep quality and well-being in non-organic sleep disorders in a controlled study.

Self-administered acupressure and hydrotherapy, according to the German non-medical naturopath and priest Sebastian Kneipp, showed little to no side effects.^[35,36,43–45]^

As there is good evidence for the effectiveness of acupuncture in patients with RLS, and some pilot studies have shown that acupressure and cold applications can reduce RLS- and sleep-related symptoms, we hypothesized that self-administered acupressure and Kneipp hydrotherapy with cold affusions could be a potential therapeutic option for patients with RLS.

### 1.2. Study aims

The aim of this clinical study is to assess the feasibility and effects of self-administered acupressure and Kneipp hydrotherapy in patients with RLS, and to gather preliminary information on both study interventions as a basis for conducting a high-quality confirmatory trial including a valid sample size calculation.

## 2. Methods

### 2.1. Study design

The HYDRAC study (HYDRotherapy and ACupressure for Restless legs syndrome) is a prospective, parallel, 3-armed, interventional, exploratory clinical study. The study will be conducted for 12 weeks per patient, including a self-treatment phase of 6 weeks and a follow-up phase for another 6 weeks with optional self-treatment (Fig. 1).

**Figure 1. F1:**
[figure not shown]
Design of the HYDRAC study. HYDRAC = Hydrotherapy and Acupressure for Restless legs syndrome.

Patients will be enrolled at the Charité Outpatient Clinic for Complementary and Integrative Medicine in Berlin-Mitte. After training on how to self-perform the respective interventions, the study interventions are to be carried out independently by the patients at home.

To ensure high-quality evidence, we will conduct this study in accordance with Standard Protocol Items: Recommendations for Interventional Trials (Table 1)^[46]^ and report our findings in accordance with the Consolidated Standards of Reporting Trial (CONSORT) Statement.^[47]^ This clinical trial was approved by the Charité Ethics Committee on 19.07.2022 (reference number: EA2/132/22) and has been registered with the German Clinical Trials Registry with an identifier (DRKS00029960) on August 09, 2022.

**Table 1 F4:**
[figure not shown]
A standard protocol items: recommendation for interventions for trials (SPIRIT).

### 2.2. Patients and recruitment

A total of 51 patients (n = 17 in each arm) included in the trial. Patients who meet the following inclusion criteria will be included in the study: age between 18 and 75 years; diagnosis of RLS confirmed by a trained medical specialist (“Facharzt”) in accordance with the diagnostic criteria,^[48]^ subjective information on the intensity of RLS symptoms greater than or equal to 30 on a visual analog scale of 0 to 100 mm in the last 7 days before inclusion; at least moderate RLS symptoms (IRLS - total score ≥ 11 according to a severity scale validated by the International Restless Legs Syndrome study group (IRLS); no planned change in medication during the study; willingness of the patient to be randomized and to participate in the examinations of the study or to fill in questionnaires/diaries; patient consent; ability to comprehend the significance and content of the study; and presence of a written informed consent form.

Patients who meet any of the following criteria are excluded: indication for iron substitution therapy (exceptions are iron substitution that has already been carried out without sufficient symptom improvement or refusal of the iron substitution therapy by the patient); regular use of RLS triggering/exacerbating medications (such as mirtazapine, mianserin, clozapine, olanzapine, risperidone, haloperidol, sulpiride, promethazine); use of hydrotherapy, acupuncture, or acupressure in the last 4 weeks prior to inclusion or planned in the next 12 weeks; acute infection with severe acute respiratory syndrome coronavirus type 2 virus or presence of long-coronavirus disease syndrome; for women: pregnant or breastfeeding; presence of a serious acute and/or chronic organic or serious mental illness that does not allow participation in the study intervention (e.g., advanced cardio/pulmonary disease New York Heart Association classification/COLD III + IV); known Raynaud disease and advanced circulatory disorders of the extremities; inadequately treated dermatological disease in the therapeutic area (large wounds, severe atopic dermatitis, severe psoriasis, etc); abuse of medicines, drugs and/or alcohol; existing treatment with opioids; participation in an intervention study during the same period of the study or in the last 3 months prior to the start of the study for this condition; dependence on the study site (e.g., employee).

The recruitment of study patients will be carried out primarily by advertising on public transport, newspaper advertisements, newsletters of medical institutions, the internet, flyers at general practitioners’ clinics, and neurological specialist practices. If patients meet the study criteria, they must sign an informed consent form before participating in the study or before randomization. The study physician obtains informed consent and signs a written informed consent form. The consent form contains the agreement to participate in the study, as well as the collection and storage of study data and personal data of the patient.

### 2.4. Study interventions

#### 2.4.1. Hydrotherapy according to Kneipp

Patients in the hydrotherapy group will be trained by the study physicians on the day of randomization and will receive an illustrated manual. Hydrotherapy should be performed semi-standardized with obligatory and optional affusions. The patients perform the treatments twice daily for 6 weeks. After week 6, further treatment is optional. Recommended affusions are 2 cold affusions up to the knees daily for 30 to 60 seconds or 3 to 6 minutes if performed as alternating warm/cold affusions. (Fig. 2) In total, this takes approximately 20 minutes daily, including preparation and post-processing time. Optional affusions include cold or alternating warm arms and cold face affusions. The optional affusions are selected by a study physician according to the physical condition and symptomatology during training on the day of randomization. Arm affusions can be used in cases of RLS symptoms in the arms, and face affusions can be used in cases of fatigue. Facultative affusions can be performed as often as desired during the day, following the basic Kneipp rules (Table 2). One and 3 weeks after the start of intervention, patients will be contacted by a study physician by phone to inquire about difficulties with implementation, to clarify any questions that have arisen, and to improve adherence to interventions. If necessary, interventions will be adjusted in terms of the application temperature.

**Table 2 T2:** General rules for hydrotherapy applications according to Kneipp (as handed out to patients).

Empirical experience indicates that the success of water treatments depends on the regular and correct way of performing them. The following basic rules should be observed:
•Do not perform the applications in cold or drafty rooms. •Do not perform cold applications on cold body/parts of the body; warm up cold hands and feet before watering, e.g., by gymnastics or a walk or even a warm bath. •After the cold applications the water should not be dried off, if possible, but only wiped off with the hands or carefully dabbed dry. Only the spaces between the toes are dried. •A few minutes after the cold-water application, the body should be completely warmed up again, so please put leggings on immediately after the applications and/or ensure good rewarming through movement or bed rest; do not remain motionless or without clothing/blanket. •Do not apply immediately before or after eating (interval approx. 30 min). •Do not smoke before, after and during the treatment; coffee, tea or alcoholic beverages also impair the reactivity of the capillary vessels and thus also the desired positive reaction. •In case of varicose veins, the water temperature of the warm application should not exceed 37°C (bath thermometer!). •A bluish discoloration of the skin and/or a cold pain are signs of cold application for too long and should be avoided. Please perform the applications only as long as it is comfortable for you. •Cold casts can be intensified by extending the watering time or repeating the affusion (e.g., arm affusion).
When should you not perform hydrotherapy treatments?
•Women should only perform applications on the upper body during menstruation. •Do not perform a knee cast during acute inflammation of the urinary tract. •In case of colds, sinusitis, and trigeminal neuralgia, do not perform facial watering. •In case of open injuries or ulcers of the body parts to be watered.

°C = degree celsius.

**Figure 2. F2:**
[figure not shown]
HYDRAC study: Scheme of the study intervention hydrotherapy according to Kneipp. HYDRAC = Hydrotherapy and Acupressure for Restless legs syndrome.

#### 2.4.2. Acupressure

Patients in the acupressure group will be trained by the study physicians after inclusion and randomization, and will also receive an illustrated manual. Acupressure should be performed in a standardized manner with a 6 acupuncture point set according to the rules and principles of Chinese Medicine,^[49]^ as well as following a modified expert consensus process. The following acupressure points are used bilaterally: Liver 3 (Liv-3), Spleen 6 (SP-6), Kidney 3 (KI-3), Stomach 36 (St-36), Pericardium 6 (PC-6) and Large Intestine 4 (LI-4) (Fig. 3). The patients carry out the treatments at least once a day for 6 weeks with a total treatment time of approximately 20 minutes daily and a duration per pressure point of approximately 2 minutes. The points can be pressed simultaneously on both sides if the patient wishes. One and 3 weeks after the start of the intervention, patients will be contacted by telephone to inquire about difficulties in practice, answer any questions that may have arisen, and improve their adherence to the intervention. If necessary, intervention (number of acupressure points) will be adjusted. After week 6, further treatment is at the patient discretion.

**Figure 3. F3:**
[figure not shown]
HYDRAC study: Scheme of the study intervention acupressure. HYDRAC = Hydrotherapy and Acupressure for Restless legs syndrome.

#### 2.4.3. Waiting list group

Patients in the waitlist group continue to take their routine medication and will not receive any additional training during the intervention and follow-up periods. They have the option to receive free hydrotherapy or acupressure training by one of the study physicians after completing the study.

Medically necessary treatments during the study are allowed for all groups. Changes in RLS medication are recorded in patients’ diaries.

#### 2.4.4. Outcomes

Patients will receive the following questionnaires, which will be completed at baseline and 6 and 12 weeks after the start of the intervention phase:

*International Restless Legs Syndrome Study Group Rating Scale for Severity of Restless Legs Syndrome*^[50]^: 1 of 3 assessments which is validated for the German language area for the assessment of RLS severity and for the characterization of RLS

*Restless Legs Syndrome Quality of Life Questionnaire (RLS-QoL*)^[51]^: An 18-item scale to assess the quality of life of patients with restless legs syndrome.

*Quality of Life Short Form 12*^[52,53]^: general health questionnaire, which refers to 8 different dimensions that allow a statement about the health status of the patients.

*Hospital Anxiety and Depression Scale*^[54]^: assesses depression and anxiety severity in patients with somatic diseases or (possibly psychogenic) physical complaints.

*General Self-Efficacy Scale*^[55,56]^: A self-assessment procedure with ten items for recording general optimistic self-beliefs.

*Visual Analogue Scale*^[57]^: measures subjective general well-being on a visual analog scale (minimum 0 to maximum 100 mm).

*Patient Global Impressions Scale—Change*^[58]^ evaluates all aspects of the patient health status and assesses whether there has been improvement or deterioration in clinical condition.

We also want to investigate whether patients perceive a change in daily activities and how they estimate the effectiveness of the intervention before randomization, the success of the therapy, and the overall effectiveness of the interventions at the end of weeks 6 and 12.

In addition, the patients keep a diary to record the frequency of the study interventions and changes in their medication daily from week 1 to week 6. In the diary, patients will also note any side effects, adverse events, or serious adverse events. The first diary, which is handed out to the patients after randomization, is kept daily from weeks 1 to 6. The second diary is mailed to patients 12 weeks after enrollment, that is, at the end of the follow-up period, and is intended to retrospectively record the last 6 weeks of voluntary intervention, that is, safety, medication use, and continuation/frequency of intervention.

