### 2.10. Oversight and monitoring

#### 2.10.1. Safety monitoring

Together with the study documents, all patients will receive the necessary contact information to report any serious events directly to the Institute of Social Medicine, Epidemiology and Health. Serious Adverse Events must be reported by the study physicians to the study management within 24 hours of being known.

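### In weeks 7–12, non-serious adverse events, RLS medication changes and voluntary use are recorded only by recall of up to six weeks, although weeks 1–6 are recorded daily

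*Protocol article*

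**What the plan says.** Section 2.4.4 (Outcomes) describes two diaries. For the first: "The first diary, which is handed out to the patients after randomization, is kept daily from weeks 1 to 6". It covers how often the intervention was used, medication changes and harms: "In the diary, patients will also note any side effects, adverse events, or serious adverse events". The second is "mailed to patients 12 weeks after enrollment, that is, at the end of the follow-up period, and is intended to retrospectively record" the six weeks just ended: safety, medication use, and whether and how often the intervention was continued.

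Section 2.4.3 (Waiting list group) makes the diaries the place for medication data in all groups: "Changes in RLS medication are recorded in patients’ diaries". For harms, section 2.10.1 (Safety monitoring) adds one further route: "all patients will receive the necessary contact information to report any serious events directly". Study physicians must then pass serious adverse events to the study management within 24 hours.

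Telephone contacts are described at one and three weeks after the start (sections 2.4.1, 2.4.2 and the Discussion). None is described in weeks 7–12. Treatment in those weeks is optional (section 2.1).

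**The concern.** The aim in section 1.2 is to "assess the feasibility and effects of self-administered acupressure and Kneipp hydrotherapy in patients with RLS". Weeks 7–12 are the only period in which patients in the two intervention arms choose for themselves whether to go on, so they bear directly on feasibility. The closing part of section 3.1 also counts what the study will show about safety at home among its advantages. Yet in this period the patient has nothing to write in until it is over.

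Three kinds of data are exposed:

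- **Minor adverse events.** Short-lived complaints are easily forgotten over several weeks.
- **RLS medication changes.** Section 2.4.3 allows medically necessary treatment in every group. A change that is forgotten or misdated makes the week 12 severity score harder to interpret.
- **Voluntary use.** A frequency reconstructed over six weeks is not the same measurement as a daily tick. The form is also completed around the time when unblinded patients rate their week 12 state, which may colour what they remember.

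The limitations in section 3.1 discuss subjective outcomes, lack of blinding and the single training session, but not this recall.

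**Working it through.** **1. The two halves side by side (from the sections cited above).**

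| | Weeks 1–6 | Weeks 7–12 |
|---|---|---|
| Diary in the patient's hands | from randomization | not until week 12 |
| Mode of entry | daily | once, retrospective |
| Telephone contact described | weeks 1 and 3 | none |
| Non-serious events | daily diary | recall |
| RLS medication changes | daily diary | recall |
| Frequency of use | daily diary | recall |
| Serious events | diary and direct report | recall and direct report |

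Only the last row has a prospective source in both halves.

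**2. Length of the recall window.** 6 weeks × 7 days = 42 days, out of 12 × 7 = 84 days; 42/84 = 50%. This is a share of calendar time. It is not a share of exposure, because all mandatory treatment falls in weeks 1–6, and it does not estimate data lost.

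**3. The plan's own numbers.** Section 2.5 gives 17 randomized per group, about 10% dropout and at least 15 remaining. This reproduces: 15/0.9 = 16.7, rounded up to 17; in reverse, 17 × 0.9 = 15.3. The present point changes neither figure. One patient is 1/17 = 5.9 percentage points of an arm, or 1/15 = 6.7. That is the resolution of any proportion in this trial, not a measure of harm from recall.

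**4. What recall loss could do (illustration only).** The documents give neither an event risk nor a recall rate. Assume 15 patients per arm, a true 20% risk of a non-serious event in weeks 7–12, and a probability *r* that an affected patient reports it. Expected reports = 15 × 0.20 × *r*; chance of at least one report = 1 − (1 − 0.20*r*)^15.

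| Recall *r* | Expected patients reporting | Chance of at least one report |
|---|---|---|
| 100% | 3.0 | 96% |
| 90% | 2.7 | 95% |
| 75% | 2.25 | 91% |
| 50% | 1.5 | 79% |

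On these assumptions, the chance of seeing at least one case holds up unless recall is poor. The observed frequency falls in proportion to *r*, from 20% to 10% at *r* = 50%.

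**5. Dropout.** About 10% of 51 is 5.1 patients before week 12; the article does not say how many of these would leave after week 6. A patient who leaves in weeks 7–12 has not yet been sent the second diary, so there is no partly completed form to recover. Section 2.7 does not replace missing data.

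**The case against.** The strongest objection is that the late mailing may protect what it measures. The Discussion says that diaries serve to promote motivation and adherence. A diary held through the optional phase could therefore prompt the use it is meant to observe. This stands as a real trade-off, although the article does not give it as the reason for the timing. It touches only the item on use. It does not apply to adverse events or medication changes, or to the waiting list arm, which has no intervention to prompt.

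Other points also stand in part. Entry requires that no medication change be planned (section 2.2), which should make changes less frequent, but section 2.4.3 still allows and records them. The trial is exploratory, and the week 12 questionnaires do not depend on the second diary. The article condenses a fuller protocol, so the absence of another source is a statement about what it describes.

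A reader might infer more than the documents support:

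- *That adverse events as a whole go unrecorded in weeks 7–12.* Serious events have a direct route throughout (section 2.10.1), and reasons for withdrawal and its timing are recorded (section 2.9).
- *That any fall in events or use after week 6 is an artefact.* Nothing quantifies recall error, and a true fall once treatment becomes optional is plausible. The two explanations simply cannot be separated.
- *That the comparison between groups is biased.* Section 2.4.4 describes the same diaries for all patients, and section 2.7 plans comparisons between groups. Recall could still differ between unblinded arms, but the documents do not show that it would.

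**Conclusion.** The point holds as a weakness of data collection in weeks 7–12, limited to non-serious adverse events, RLS medication changes and voluntary use. For these, the article describes only a single retrospective entry covering up to 42 days, plus the time the form spends in the post, after six weeks of daily recording. Minor events may be under-recorded, medication changes may be misdated, and contrasts between weeks 1–6 and weeks 7–12 may partly reflect the change of method. How large the error is cannot be derived from the documents; the illustrative range rests on assumed risks and recall rates. No sample size, estimate or planned test changes. The change is worth making because it is small and improves the safety and feasibility data that the trial is meant to deliver, not because a result is shown to be wrong. This assumes that the full protocol has no further prospective source for weeks 7–12.

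**What to change.** Hand out or mail the second diary at week 6, in all three arms, and collect it at week 12. Keep it brief and prospective, for example one entry per week: any adverse event, any change in RLS medication with its date, and, in the intervention arms, a minimal item on use.

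The form and its dispatch are already planned, so the change is mainly one of timing. If it can go out with the week 6 questionnaires, no extra mailing is needed; the article does not say how those are delivered. Visits, sample size and analyses stay as they are.

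The downside is that the use item may slightly prompt voluntary use. If the sponsor regards that as important, leave that item retrospective at week 12 and make only the adverse event and medication items prospective.

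For whatever remains on recall, and for patients already past week 6, report weeks 7–12 separately from weeks 1–6, do not read differences between the two periods as changes over time without that caveat, and name the recall in the limitations.
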